### Participants

#### Inclusion criteria

Office systolic blood pressure (SBP) from 140 to 159 mm Hg and/or diastolic blood pressure (DBP) from 90 to 99 mm Hg for patients who did not take antihypertensive drugs previously, or office SBP from 120 to 159 mm Hg and/or DBP from 80 to 99 mm Hg for patients who did not change antihypertensive drugs at least 1 month.Aged between 18 and 65 years (male or female).Answering and completing the questionnaires.Using smart phone.Written informed consent.

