### Interventions

#### Usual care group

All patients will be provided usual care at the respective community health service centre, in conjunction with any ongoing care that they are receiving from their family doctor. Patients at high or very high cardiovascular risk will receive antihypertensive drugs according to the recommendation of the guidelines,^9 10^ including diuretics, β-blockers, calcium channel blockers, angiotensin receptor blockers and ACE inhibitors. The choice of antihypertensive drugs will be individualised, with consideration of patients’ coexisting conditions and adverse effects to the medications. Research team will engage in consistent communication with each patient’s family doctor, including a standard letter conveying the reminder that the doctor is free to implement any additional therapies that are deemed to be appropriate, including increase or decrease the type and dosage of antihypertensive drugs. Research team will also send education materials to all patients. Content will include information about hypertension, its clinical features, epidemiology, diagnostic criteria and treatment options, as well as the role and suggestions of lifestyle intervention in hypertension.

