### Statistical analysis

A full analysis set, a per-protocol set and a safety set will be used in this trial. The full analysis set will consist of all randomised patients according to the intention-to-treat principle. The full analysis set will be the primary analysis, and all analyses will be conducted for this population if not otherwise stated. The per-protocol set will include those who complete all follow-ups on time and without major violations. Major violations include but are not limited to not ineligibility according to the inclusion and exclusion criteria, receiving medicines that affect blood pressure except antihypertensive drugs, or not completing ≤38 sessions TEAS (80% of prespecified 48 sessions). The per-protocol set will be the secondary analysis set and will be used for the sensitivity analyses for the primary outcome. All those who receive at least one session of TEAS will be defined as the safety set, which is used for the safety analyses.

Baseline characteristics will be summarised by groups. Continuous variables will be described using the mean (SD), or the median (IQR) if the normality assumption is violated. Categorical variables will be described using the frequency (percentage). The significance level of superiority test will be set at one-sided 0.025 for the primary outcome. The significance level will be set at two-sided 0.05 for secondary outcomes. All analyses will be carried out using SAS V.9.3.

The change from baseline in office SBP at week 12 will be analysed by a mixed-effect model using baseline value as a covariate, treatment group as a fixed effect, and community and interaction between community and treatment as random effects. Multiple imputation will be used for missing data.^30^ For the secondary and tertiary outcomes, continuous variables will be compared at all follow-up time points using a mixed-effect model with repeated measurement methods. If there is a normality violation in the continuous variables, a transformation will be performed before the test. Categorical variables will be compared using a generalised linear mixed-effect model. The consistency of treatment effects on the primary outcome will be explored in predefined subgroups, including sex, education and taking antihypertensive drugs or not and urban or rural community.

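### The primary model adjusts for baseline SBP only; adding baseline antihypertensive drug use, which defines the two entry populations, is a nearly free precision gain and not a correction of an error

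*Protocol article*

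**What the plan says.** The Statistical analysis section of the protocol article gives the primary model term by term: "The change from baseline in office SBP at week 12 will be analysed by a mixed-effect model using baseline value as a covariate". Treatment enters as a fixed term, with "community and interaction between community and treatment as random effects". Baseline SBP is the only covariate named.

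The Inclusion criteria set two routes of entry. The first, open to patients never treated before, is "Office systolic blood pressure (SBP) from 140 to 159 mm Hg and/or diastolic blood pressure (DBP) from 90 to 99 mm Hg". The second is "office SBP from 120 to 159 mm Hg and/or DBP from 80 to 99 mm Hg for patients who did not change antihypertensive drugs" for at least a month.

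Drug use appears once more in the Statistical analysis section, among the "predefined subgroups, including sex, education and taking antihypertensive drugs or not and urban or rural community". Under Randomisation and masking, the sequence is stratified by district and by nothing else. Under Usual care group, "Patients at high or very high cardiovascular risk will receive antihypertensive drugs according to the recommendation of the guidelines", and family doctors in both arms are free to add to or reduce drug treatment.

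**The concern.** Baseline drug use is the one patient characteristic, apart from blood pressure itself, on which the entry rule turns. If it predicts the 12-week SBP change beyond what baseline SBP already predicts, leaving it out puts explainable variation into the error. Part of that variation lies between centres if the share of untreated patients differs from centre to centre. That part is the costly one in a cluster trial, because a shift common to a centre does not average out over its patients.

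There are three plausible sources of a residual difference at equal baseline SBP:

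- **Underlying means.** Regression to the mean at a given reading depends on the mean of the population the patient comes from, and this may differ between treated and untreated patients.
- **The and/or DBP rule.** An untreated patient with SBP 130 qualifies only with DBP 90–99. A treated patient with SBP 130 qualifies on SBP alone. Equal SBP therefore does not mean the same kind of patient.
- **Scope for drug change.** Untreated patients at high risk can be started on drugs, whereas treated patients had been on an unchanged regimen for at least a month.

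At stake is precision. The test is made against a 4 mm Hg margin with 6 mm Hg expected, so only 2 mm Hg separates the assumption from the null.

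**Working it through.** **Inputs from the protocol article (Sample size calculation):** expected difference 6 mm Hg, margin 4 mm Hg, SD 10 mm Hg, two-sided 5% level (the same critical value as the one-sided 2.5% test), ICC 0.01, 40 analysed patients per centre, 14 centres per arm after losses.

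**Inputs not in the document, assumed here:**
- d, the untreated/treated difference in mean SBP change at equal baseline SBP: 0, 2, 3 or 5 mm Hg.
- p, the untreated share: 0.30.
- s, the SD of that share between centres: 0, 0.10 or 0.15.

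**Step 1: the plan's own figures.** Net difference 6 − 4 = 2. n per group = 2 × (1.960 + 0.842)² × 10² / 2² = 392.4, which matches the stated 392. The design effect is 1 + 39 × 0.01 = 1.39, and 392 × 1.39 = 545, which 14 centres of 40 (560) cover.

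**Step 2: power of the planned model.** Total variance 100 splits into 1 between and 99 within centres. The two random community terms together carry the between-centre part.

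Var(difference) = (2/14) × (1 + 99/40) = 0.4964, so SE = 0.705. Power = Φ(2/0.705 − 1.96) = 81.0%. With a t distribution on 26 df it is 78.0%.

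**Step 3: add baseline drug use.** The covariate removes p(1−p)d² of variance in all. Of this, s²d² comes from the between-centre part and the rest from the within-centre part:

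Var = (2/14) × [(1 − s²d²) + (99 − p(1−p)d² + s²d²)/40]

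Example, d = 3 and s = 0.10: the total removed is 0.21 × 9 = 1.89, of which 0.09 is between and 1.80 within. Var = (2/14) × (0.91 + 97.20/40) = 0.477, SE 0.691, power 82.5%.

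| d (mm Hg) | s | Variance ratio | SE | Power (normal) | Power (t, 26 df) |
|---|---|---|---|---|---|
| 0 | any | 1.000 | 0.705 | 81.0% | 78.0% |
| 2 | 0 | 0.994 | 0.702 | 81.3% | 78.3% |
| 2 | 0.10 | 0.983 | 0.698 | 81.7% | 78.7% |
| 2 | 0.15 | 0.969 | 0.693 | 82.2% | 79.3% |
| 3 | 0 | 0.986 | 0.700 | 81.5% | 78.6% |
| 3 | 0.10 | 0.961 | 0.691 | 82.5% | 79.6% |
| 3 | 0.15 | 0.930 | 0.679 | 83.7% | 80.9% |
| 5 | 0 | 0.962 | 0.691 | 82.5% | 79.5% |
| 5 | 0.10 | 0.892 | 0.665 | 85.2% | 82.5% |
| 5 | 0.15 | 0.804 | 0.632 | 88.6% | 86.1% |

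**Step 4: do the different SBP cuts alone create a residual d?** Take one population for both routes (assumed true mean 138, true SD 12, measurement SD 8), with entry at 140–159 for one group and 120–159 for the other, and the entry reading used as baseline. The expected change at reading x is −[64/(144 + 64)] × (x − 138) = −0.308 × (x − 138), whichever cut applied. In simulation the raw mean changes are about −3.1 and −0.3 mm Hg, but after the single baseline-SBP covariate the group difference is within 0.03 mm Hg of zero. The planned model removes this effect.

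If the underlying means differ by Δ, the residual is 0.308 × Δ in the same setting. A residual of 2 mm Hg from this source alone would need means 2/0.308 = 6.5 mm Hg apart.

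**The case against.** The strongest reply is that nothing here is stated wrongly. In a linear mixed model of a randomised trial, omitting a baseline covariate leaves the treatment estimate unbiased and the test valid. The plan already adjusts for the baseline value of the outcome, and no printed figure changes. All of that stands.

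It can also be said that the size rests on three values the document does not give. That stands too. With d of 2–3 mm Hg and s of 0–0.05 the gain is under one power point. The top figure, 88.6%, needs drug use alone to supply 0.56 of the assumed between-centre variance of 1.0.

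A reader might go further than the documents allow in four ways:

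- **That the higher SBP cut for untreated patients leaves regression to the mean which one slope cannot absorb.** Step 4 shows that it does not. The and/or DBP wording also lets untreated patients in with SBP below 140, so the SBP ranges overlap more than they first appear to.
- **That untreated patients must fall further because drugs can be started.** The Usual care group section lets doctors raise or lower treatment for any patient, so neither the direction nor the size is established.
- **That chance imbalance in drug use is a further harm on top of the wider standard error.** It is the same variance, already inside the SE of 0.705. With two centres per district and allocation stratified by district, differences in drug use between districts are largely balanced as well.
- **That the imputation model and the secondary models omit drug use.** The article does not list their covariates, and those may be in the statistical analysis plan, which is not at hand.

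What the reply does not remove is that the article fixes the primary model with a single covariate, while a second one is known for every patient, is already considered relevant by the sponsor, and is balanced neither by stratification nor by adjustment.

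**Conclusion.** The point holds as an optional improvement in precision, not as an error of validity. The gain runs from nil, if baseline SBP captures everything, through about one to three power points for a residual difference of 2–3 mm Hg, to at most about eight points for 5 mm Hg with strong variation in drug use between centres. The lower part of that range is the safer expectation, because the document supports only the plausibility of a residual difference and not its size. These figures assume 30% untreated patients and take the plan's SD of 10 and ICC of 0.01 as the variance left after adjustment for baseline SBP.

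**What to change.** In the Statistical analysis section, or in the statistical analysis plan before unblinding, name two fixed covariates for the primary model: baseline SBP and baseline antihypertensive drug use (yes/no). Define the second from the status recorded at entry, before randomisation. Drug use during follow-up must not be used, since treatment may affect it. If the statistical analysis plan already lists this covariate, it is enough to align the model as described in the article.

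The cost is one line of text and one degree of freedom among about 1,600 patients. The variable is already needed for the entry rule and the predefined subgroup. Fixing it in advance also avoids a data-driven appearance if it were added only after an imbalance was seen.

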### Data management and quality control

Data will be collected by using a web-based Research Electronic Data Capture system (https://yu.life.sjtu.edu.cn/redcap/) developed by Shanghai Jiao Tong University. All researchers will receive training about data input, inquiry and modification. Independent data managers will check the system to ensure the integrity, accuracy and timeliness of data. Any modifications of the data can be traced in the Research Electronic Data Capture system. Moreover, patient information will be anonymous, including name, ID number and telephone number, to protect privacy. After the trial is completed, this system will be locked by the data management team. Then the researchers can no longer modify the data. An independent data and safety monitor board will be established to review and interpret the trial data every 6 months.

### Patient and public involvement

The first author ([name]) and other coresearchers in community health service centres are patients with hypertension. They were involved in the design and conduct of the trial. During the design stage, choice of outcome measures, the number of study visits and methods of recruitment were determined by discussions with patients. Once the trial has been published, a brief summary of the findings will be presented to attendees in the community health service centres.

### Ethics and dissemination

This study conforms to the principles of the Declaration of Helsinki. The study protocol (version number: 2.0; 13 June 2020) was approved by the ethics committee of Beijing University of Chinese Medicine (No. 2020BZHYLL0104). Meanwhile, written informed consent will be obtained by the clinical research coordinator from all patients before randomisation. Results of the trial are expected to be published in a peer-reviewed journal.

## Discussion

To our knowledge, this is the first cluster randomised trial to investigate the effectiveness and safety of the smart phone-based TEAS as adjunctive therapy for hypertension.

This study is a community-based cluster randomised trial. There are several advantages for this design. First, contamination is one of the common biases, but it can be alleviated by the cluster design because only the communities randomly assigned to the TEAS group will have access to the instrument. Furthermore, communities were chosen with adequate geographical separation from each other. Second, patients will be recruited from their homes or communities. Unlike hospital-based studies, which only include those who seek medical help, our design will overcome the traditionally low detection of hypertension.

The TEAS in this trial can be received through smart phone at home by the patients themselves. The majority of hypertension patients had to travel by taxi or use public transportation to attend physician visits and prescribe antihypertensive drugs. If the effectiveness of TEAS is verified, this non-pharmaceutical therapy will result in additional savings of cost and burden. The time, expense and lost wages are also identified as barriers for controlling blood pressure. The smart phone-based TEAS at home may contribute to improving treatment adherence. Furthermore, several patients sometimes forget to take medicine, especially when they are busy working or tripping. As we mentioned before, we could use the background of TEAS software to recognise patients with poor compliance real timely and remind them to complete treatment.

The mechanism of acupuncture to reduce blood pressure is still unclear. It was found that TEAS could decrease sympathetic nervous system activity and increase parasympathetic nervous system activity,^31^ which may contribute to reducing blood pressure. Moreover, TEAS was shown to have a vasodilator effect.^32^ Our animal experiments also indicated that mitogen-activated protein kinases and β-adrenergic receptors were involved in the mechanism of acupuncture’s amelioration of hypertension.^33 34^

Our study has several limitations. First, blinding for patients was not feasible; however, several steps will be implemented to minimise potential biases. Outcome assessors will be masked and an electronic data capture system with tablet has been developed to separate streams of data collection processes. Moreover, the blood pressure recordings were from automated devices to minimise biases for the key outcome. Second, surrogate outcomes are used in this study. There is a good evidence to support improved clinical outcomes with the reductions in blood pressure shown in other trials.^35 36^ To show a benefit in clinical events, a much larger and longer trial would be required. Third, patients in the usual care group will be screened for cardiovascular disease risk at baseline, have their blood pressure assessed and be provided with information about hypertension education. After being aware of their elevated blood pressure, some patients in the usual care group might modify their behaviour and receive more treatment than clinical practice. This modification might reduce the real differences between the groups, which means that we may underestimate the effectiveness of TEAS.

This trial may provide high-quality evidence for the effectiveness of the smart phone-based TEAS as adjunctive therapy for hypertension. If the study hypothesis is confirmed, smart phone-based TEAS may help to attain the United Nations General Assembly Action Plan for a one-third reduction in premature mortality from cardiovascular disease.

### Trial status

Recruitment was started on 18 November 2020 and is expected to close in June 2022.
